### Study population

All infants born with birth weight between 1.0 and < 1.8 kg, enrolled in the main trial, who survive the neonatal period, and whose parents consent for their participation in the follow-up study, are eligible to be enrolled.

All infants who die within the first month of life or whose parents refuse consent for follow-up will be excluded from the study.

We employ two strategies to approach the parents for enrolment. First, we approach the mother/parent during the 29-day follow-up visit for the main trial. The second strategy is for children who have completed the 29-day follow-up visit in the main trial. For these children, we approach the mother/parent either telephonically or when they visit the high-risk infant follow-up clinic as part of standard hospital care. A verbal preconsent is taken and an in-person hospital visit is scheduled for a detailed written informed consent for participation in the follow-up study.

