### Sample size calculation

The sample size for the main iKMC trial was a total of 4200 neonates. Early completion in January 2020 led to a total of 3211 neonates being enrolled in the main iKMC trial. A preliminary review of literature of neurodevelopment in infants between 1 and < 1.8 kg shows the prevalence of any of the conditions of cerebral palsy, hearing impairment, vision impairment, and mean development scores to vary from 5 to 25% [25–27]. Any neurodevelopmental impairment (e.g., cerebral palsy, Bayley score < 85, hearing or vision impairment) in the study population is estimated to be approximately at 15–25%. We estimated the sample size for comparison of the risk of neurodevelopmental impairment in control and intervention groups (20% compared with 15% or 25% [25% lower or higher]) with 80% power and a significance level of 5% to be 1100 per group, requiring a total of about 2200 children.

We thus propose to enroll 2200 babies from the main trial to reach the above-mentioned sample size.

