**Secondary outcomes**			
Mortality	Screen for death of enrolled child occurring any time between 29 days and 3 years of age	Mortality/survival status at each screening point. Assessments performed every 3 months until the age of 3 years	
Growth	Anthropometric parameters of weight (W), length (L), and head circumference (HC) for age using standardized equipment	Anthropometry at 6, 12, and 24 months of age. Parameters are plotted as per corrected age on WHO Multicentre Growth Reference Study (MGRS) charts and interpreted as per *z* scores Postnatal growth failure defined as fall in *z* scores or *z* scores < 2 SD	Measurements are obtained during facility visits. In case the participant is unable to visit the facility, we perform the measurement at the home of the participant
Feeding practices	Assessment of breastfeeding, expressed breast feeds, complementary feeds at 6 months, and adequacy of feeding beyond infancy	Feeding practices measured through a standard questionnaire at each follow-up visit—every 3 months until the age of 3 years	
Maternal depression	Patient Health Questionnaire 9 (PHQ-9)	Maternal depression measured using PHQ-9 at 6 and 12 months of age	Literature suggests, while early screening for post-partum depression is important, additional screening points at either 6 or 12 months can capture additional women who may have initially screened negative at earlier time points. Therefore, we have included these time points in this study [48]
Home environment	HOME	Assessment of home environment measured using standard HOME-SF scale at 18 months by a home visit	HOME is a validated tool across cultures. The HOME-SF scale has 6 subscales: (1) parental responsivity, (2) acceptance of the child, (3) organization of the environment, (4) learning materials, (5) parental involvement, and (6) variety in experience These align with the MAL-ED study which has also identified that a three-factor structure—emotional and verbal responsivity, clean and safe environment, and child cleanliness—can be examined cross-culturally [49]

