### General principles for analysis

The analysis will be by intention to treat. The primary outcome is a composite outcome comprising cerebral palsy, hearing impairment, vision impairment, cognitive, language, socio-emotional, adaptive and motor impairment, and epilepsy, and the presence of any one or more will be considered as neurodevelopmental impairment. However, during analyses, we will also consider each of these outcomes individually. Table 1 includes the scale/tool used for outcome measurement and wherever appropriate, the cutoffs of the scales, to indicate the presence or absence of the neurological impairment.

The primary and secondary outcomes will be compared between the intervention and control groups. All planned analysis will use a 5% significance level. Risk ratios and their confidence intervals will be calculated and will be the primary analysis if the loss to follow-up is 2.5% or lower. In case the loss to follow-up for the primary outcome is greater than 2.5%, we will additionally calculate hazard ratios and their confidence intervals. Additionally, we will adjust the results for confounding using multiple logistic regression and Cox proportional hazards models if there are any important differences in baseline characteristics between immediate KMC and control groups.

If more than 5% of data is missing from interim assessments, multiple imputation will be performed, accounting for clustering by country with the number of imputations based on the percentage of missing data. Subgroup analysis will be conducted by (i) birth weight categories (1 to < 1.2 kg, 1.2 to < 1.5 kg, and 1.5 to < 1.8 kg), (ii) gestation (< 34, 34–36, >=37 weeks), and (iii) singleton/multiple birth. Secondary analysis will be limited to an analysis by compliance. This secondary analysis will present the efficacy of the intervention by average duration of skin-to-skin contact over the first 3 days of life, categorized as > =20 h/day, 10–19 h/day, and < 10 h/day.

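### The growth-failure definition in Table 1 lacks the minus sign on 2 SD and counts a fall in z score of any size, so chance falls can supply most cases

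*Protocol article*

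**What the plan says.** Growth is a secondary outcome. In Table 1 of the protocol article the tool is "Anthropometric parameters of weight (W), length (L), and head circumference (HC) for age using standardized equipment", and the schedule is "Anthropometry at 6, 12, and 24 months of age". The same row says "Parameters are plotted as per corrected age on WHO Multicentre Growth Reference Study (MGRS) charts and interpreted as per" z scores. It then gives a binary rule: "Postnatal growth failure defined as fall in" z scores, or z scores less than 2 SD. The limit is printed with no minus sign and no word such as below. The fall has no minimum size, no pair of visits and no named measure, and the two limbs are joined by a plain or.

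Under General principles for analysis, "The primary and secondary outcomes will be compared between the intervention and control groups", with risk ratios and a 5% level. Nothing elsewhere in the article corrects or narrows the growth-failure rule.

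**The concern.** The rule is stated as a case definition, and neither limb separates poor growth from ordinary growth as written. Without its sign, the 2 SD limb takes in almost every child. The sign is easily restored, but the fall limb remains. A child tracking steadily along a centile will show a small drop between two visits about half the time, simply from measurement error and normal fluctuation. Because of the or, each such drop makes a case.

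Two consequences follow. The reported frequency of growth failure could be several times the frequency of z below -2. And the chance falls occur in both arms, so they can pull the risk ratio towards 1 and hide a real difference in attained size. Growth beyond the neonatal period is also part of the evidence that the Background section offers in support of policy change.

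**Working it through.** **Inputs from the article.** Three measures; visits at 6, 12 and 24 months; birth weight 1.0 to under 1.8 kg; sample size "with 80% power and a significance level of 5% to be 1100 per group". It gives no mean z, SD, between-visit correlation or growth effect, so those are assumptions below.

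**The plan's own figure.** The 1100 belongs to the primary outcome. For 20% versus 25%, two-sided 5%, 80% power:

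n = [1.96·√(2·0.225·0.775) + 0.8416·√(0.20·0.80 + 0.25·0.75)]² / 0.05² = (1.1575 + 0.4961)² / 0.0025 ≈ 1094 per group.

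This reproduces the 1100. The growth definition does not enter it.

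**Step 1: the 2 SD limb as printed.** In the reference population, P(z < 2) = Φ(2) = 97.7%. With mean z -1 and SD 1.1 it is Φ(3/1.1) = 99.7%. With the sign restored, the second population gives P(z < -2) = Φ(-1/1.1) = 18.2%.

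**Step 2: add a fall of any size, sign restored.** One measure, net change from 6 to 24 months, mean z -1 and SD 1.1 at both visits, correlation 0.7:

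- SD of the change = 1.1·√(2·(1 - 0.7)) = 0.852. Its mean is 0, so P(fall) = 50.0%.
- Correlation of the 24-month z with the change = √((1 - 0.7)/2) = 0.387, so P(z < -2 and fall) = 13.2% (bivariate normal).
- P(case) = 18.2 + 50.0 - 13.2 = 55.0%.

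Of these, 50.0 - 13.2 = 36.8 points, about two thirds of all cases, come from a fall alone.

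**Step 3: other readings of the same sentence.** Simulation with SD 1, mean z -1 or -1.5, adjacent-visit correlation 0.7 to 0.85, correlation 0.5 between measures, sign restored:

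| Reading | No mean change | Catch-up of 0.2 to 0.4 z per interval |
|---|---|---|
| One measure, net fall 6 to 24 months | 53% to 60% | 16% to 41% |
| One measure, fall over any interval | 83% to 89% | 54% to 82% |
| Any of three measures, any interval | 97% to 99% | 83% to 98% |

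**Step 4: power at 1100 per arm, model of step 2.** The control rates are 18.2% (z < -2) and 55.0% (z < -2 or any fall). Power ≈ Φ((d - 1.96·SE₀)/SE₁), where d is the difference in proportions, SE₀ its pooled standard error and SE₁ its unpooled standard error.

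| Benefit at 6, then 24 months | z < -2 alone | Power | z < -2 or any fall | Power |
|---|---|---|---|---|
| 0.2, 0.2 | 13.8% | 80% | 53.5% | 11% |
| 0.1, 0.2 | 13.8% | 80% | 49.4% | 75% |
| 0, 0.2 | 13.8% | 80% | 45.4% | 99% |

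First row, combined rule: d = 0.0149 and both standard errors are 0.0212, so Φ((0.0149 - 0.0416)/0.0212) ≈ 0.10, or 0.11 with the opposite tail. A constant shift leaves each child's change the same in both arms, so the fall limb adds cases but no signal. When the benefit accrues between visits, the fall limb carries signal.

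**Step 5: the z score itself.** A 0.2 difference in mean z at 1100 per arm has 97% power at SD 1.2 and 99.7% at SD 1.0.

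Steps 4 and 5 assume that all 1100 children per arm are measured.

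**The case against.** A reader might infer that nearly every child will be a case and that the growth comparison cannot detect an effect. The documents do not support that, for four reasons.

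- The near-100% figure for a single measure depends on the missing sign. No analyst would code a child well above the reference median as growth failure, so the printed limit is almost certainly a slip. With the sign restored, near-100% needs a fall in any of three measures over any interval, and the article does not say that the measures are pooled.
- The power loss depends on the shape of the effect. It is severe for a constant shift and small or absent for a benefit that builds up. In the last row of the power table the criticised rule does better than z below -2 alone.
- Growth is not only this binary. The same row interprets the measurements as z scores, and comparing those is well powered.
- The size of the fall, the visits and the measure could be set out in the full protocol or analysis plan, which are not shown.

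The first three stand, and they limit the claim. The fourth stands in part. A condensed article may leave detail out, but this one states a rule, and applied as stated that rule admits chance falls. If a fuller document gives a threshold, Table 1 needs to agree with it.

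**Conclusion.** The definition is faulty as stated and should be corrected. The 2 SD limit needs its minus sign. The fall limb needs a size and an interval, or should go. With the sign restored, about half of children or more are cases if z changes centre on zero: 55% for one measure from 6 to 24 months, more under the wider readings, and as few as 16% for a net fall with catch-up growth. So wide a range from one sentence means the reported frequency could not be interpreted. Power for a constant 0.2 z benefit drops from about 80% to about 11%, but it is 75% to 99% when the benefit builds up.

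The 97.7% is a plain normal tail area. The other rates and powers depend on assumed means, SDs and correlations, because the article gives none. The point concerns one derived measure of a secondary outcome and does not touch the primary outcome or the sample size.

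**What to change.** In the Growth row of Table 1, and in the analysis plan if it repeats the rule:

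1. Define growth failure as a z score below -2 SD (WHO MGRS, corrected age), separately for weight, length and head circumference, at one named visit.
2. Delete the fall in z scores, or give it a prespecified minimum size and the two visits compared, and report it separately instead of joining it by or.
3. Name the between-arm difference in mean z score as the main growth comparison, with the binary measure in support.

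This changes a few words and needs no new data. The cost is a lower reported frequency of growth failure. If the fall limb is dropped, the binary measure also gives up its sensitivity to a benefit that accrues between visits; a separately reported fall with a stated size would keep some of that.

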### Blinding

While the main iKMC trial evaluating the impact on newborn survival did not incorporate blinding due to the nature of the intervention, during the follow-up assessments, evaluators conducting the standardized assessments are blinded to whether the child received the intervention or not to decrease the bias.

### Study implementation strategy

The iKMC follow-up study is being conducted in a standardized manner across all the sites in the five countries. Each site has constituted dedicated multidisciplinary teams to perform the different activities—study conduct, internal quality control, project management, and data management. The conduct team responsible for consent as well as follow-up of the enrolled children for outcome measurements comprises research assistants, clinical psychologist, audiologist, and field workers. The investigators who are clinicians are responsible for overall study conduct and quality assurance and quality control. Each team member is trained in the protocol, Good Clinical Practice (GCP), and study-specific standard operating procedures specific to their role and responsibility. A site coordinator is responsible for coordinating the implementation of the follow-up study at each site. A central team led by WHO headquarters coordinates the conduct across all sites, ensures harmonization of processes, and monitors quality and study progress.

### Infrastructure

An important fallout of the study has been infrastructure development. Each site has developed a designated child development assessment unit. The unit has separate designated areas for registration and screening, consent, anthropometry, structured neurological assessment using HINE, developmental assessment using BSID III, visual acuity using Teller Acuity Cards, hearing assessment using auditory brainstem responses, and data entry and management.

### Enrolment and outcome measurements

The study conduct research staff is responsible for consent as well as follow-up of the enrolled children for outcome measurements.

They are blinded to the intervention or control group allocation of enrolled children as they were not involved with intervention delivery during the main trial conduct. The staff performing outcome assessments had an initial intensive training on the standardized and validated tools being used for assessing primary and secondary outcomes of the follow-up study described in Table 1. For any identified neurodevelopmental impairment, an appropriate standard of care management is provided to the child.

### Quality assurance and quality control

The study has a well-structured quality assurance plan that is being implemented at all sites. The site coordinators ensure adherence to the manual of operations. The study has employed several checks to ensure the quality of all aspects of the follow-up study including the consent process and the outcome measure assessments. Internal quality checks are conducted by the site coordinators and study principal investigators (PIs) at each site. The data acquisition for the outcome measurements is verified by the site coordinator. Ten percent of the data acquisition is reviewed by the expert investigator/designee for completeness and consistency. The investigators monitor at least 10% of processes being performed for different outcome measurements by the study conduct team. The observations are documented in specifically designed forms. Appropriate corrective and preventive actions are taken based on expert observations. External oversight and support is provided by WHO headquarters to ensure the quality of study implementation. This is done through site visits by WHO staff or consultants using a standardized monitoring checklist. Additionally, sites transfer data to WHO headquarters every month and this data is reviewed by the central team at WHO for quality, and feedback for improvement is provided to the PIs at respective sites.

### Training and standardization

The research staff including the conduct team, project management team, data management, and internal quality control team underwent an intensive training before the start of the study. All were oriented to the protocol and GCP guidelines. Orientation and sensitization of regular health care staff of the Departments of Pediatrics, Physical Medicine and Rehabilitation, Ophthalmology and Ear, Nose and Throat regarding the study and its processes was done to ensure smooth functioning. The research staff has been provided role-specific intensive training and standardization. The research assistants and coordinators from the conduct team were trained on screening for eligibility, administering written informed consent from the parents, enrolment, outcome measure assessments, and scheduling and tracking for the 3-year follow-up of the children to minimize deviations and non-compliance to the follow-up time points. All research staff were trained in rapport building and communication with the mother and the families. Training for specific outcome measurements like visual acuity using Teller Acuity Cards, hearing using screening ABR, and maternal depression using the 9-question patient health questionnaire (PHQ-9) was provided to the designated staff. There was a 2-week intensive training for Bayley’s assessment by experts. A training of trainers (TOT) workshop for standardization of anthropometry measurements of length, head circumference, and weight was conducted by experts and the Safdarjung hospital, India investigators for all the five study sites. Each site was trained in the implementation of each tool, counseling of families if a neurodevelopmental impairment is identified with an appropriate referral system in place, and training local providers at each site.

All participating hospitals are supported to make quality-of-care improvement and provide standard of care with breast milk feeding support, complementary feeding support, and attention to hygiene for all infants.

### Data collection

The data for the study is being collected on paper-based case report forms which are transcribed into an electronic database. The electronic database has been developed on a clinical data management platform “REDCap” with all the data quality checks. The questions, response options, variable names, and data structure are identical for all sites. Double data entry is done at each site by trained entry personnel. The data manager at each site is responsible for data quality checks, query management, and ensuring completeness of data. Any discrepancies are addressed within 24 h of data collection. All data collected is password protected and stored in a local server in each site. No personal identifiers are entered in the database. All paper forms are stored in locked filing cabinets at the respective sites.

### Data management and analysis

The data management is coordinated centrally by a team from WHO headquarters, but each site is responsible for site data management and data security. A central data repository has been created at the WHO headquarters. Sites share cleaned data every month to WHO where additional checks are run and a list of queries sent to the sites for clarification. All data sent to WHO does not have any personal identifiers.

The data from this multicenter study will be accessible to all the participating research teams to jointly answer the study questions. After the publication of the manuscript reporting the results on primary and secondary outcomes, the data will be made publicly accessible.

### General principles for analysis

The analysis will be by intention to treat. The primary outcome is a composite outcome comprising cerebral palsy, hearing impairment, vision impairment, cognitive, language, socio-emotional, adaptive and motor impairment, and epilepsy, and the presence of any one or more will be considered as neurodevelopmental impairment. However, during analyses, we will also consider each of these outcomes individually. Table 1 includes the scale/tool used for outcome measurement and wherever appropriate, the cutoffs of the scales, to indicate the presence or absence of the neurological impairment.

The primary and secondary outcomes will be compared between the intervention and control groups. All planned analysis will use a 5% significance level. Risk ratios and their confidence intervals will be calculated and will be the primary analysis if the loss to follow-up is 2.5% or lower. In case the loss to follow-up for the primary outcome is greater than 2.5%, we will additionally calculate hazard ratios and their confidence intervals. Additionally, we will adjust the results for confounding using multiple logistic regression and Cox proportional hazards models if there are any important differences in baseline characteristics between immediate KMC and control groups.

If more than 5% of data is missing from interim assessments, multiple imputation will be performed, accounting for clustering by country with the number of imputations based on the percentage of missing data. Subgroup analysis will be conducted by (i) birth weight categories (1 to < 1.2 kg, 1.2 to < 1.5 kg, and 1.5 to < 1.8 kg), (ii) gestation (< 34, 34–36, >=37 weeks), and (iii) singleton/multiple birth. Secondary analysis will be limited to an analysis by compliance. This secondary analysis will present the efficacy of the intervention by average duration of skin-to-skin contact over the first 3 days of life, categorized as > =20 h/day, 10–19 h/day, and < 10 h/day.

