### Study setting

As this study is a follow-up of the concluded and recently published iKMC trial [12], the study is being conducted at the same five LMIC study sites encompassing hospitals in Ghana, India, Malawi, Nigeria, and Tanzania. The selected facilities are tertiary care hospitals that care for small and sick newborns with a high proportion of LBW babies and follow-up high-risk newborns. As part of standardization across the involved study sites, prior to the study, trainings and standardization assessments were done to ensure all participating sites could offer the WHO minimum package of care for small and sick newborns [11].

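### Covariate adjustment hangs on an undefined baseline imbalance, and its logistic result is not on the planned risk-ratio scale

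*Protocol article*

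**What the plan says.** All of the analysis rules below are in the protocol article, General principles for analysis.

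- Main measure: "Risk ratios and their confidence intervals will be calculated and will be the primary analysis if the loss to follow-up is 2.5% or lower". Above that level of loss, "we will additionally calculate hazard ratios and their confidence intervals".
- Adjustment: "we will adjust the results for confounding using multiple logistic regression and Cox proportional hazards models if there are any important differences in baseline characteristics". The sentence compares the two trial arms. The article gives no threshold for an important difference and no list of covariates.
- Country appears in the handling of missing data: "multiple imputation will be performed, accounting for clustering by country".
- Multiple births appear as the third subgroup factor, "iii) singleton/multiple birth", after birth weight and gestation.

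Elsewhere in the article, Study setting names the "same five LMIC study sites encompassing hospitals in Ghana, India, Malawi, Nigeria, and Tanzania". Study population restricts enrolment to infants who survived the neonatal period and whose parents consent. Background reports neonatal mortality of 12.0% and 15.7% in the intervention and control arms of the parent trial.

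**The concern.** Two features of the adjustment rule are fixed badly by what the text states.

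First, the trigger. Adjustment happens only if someone, having seen the baseline table, judges a difference to be important. The existence of the adjusted result is therefore data-dependent. A covariate list in a separate analysis plan would not cure this, because the condition itself would remain. The weakness matters more here than in an ordinary randomised comparison. The analysed children are those who survived and whose parents agreed to follow-up, and survival differed by arm. A prognostic difference between the groups could be a product of selection, so adjustment for known prognostic factors is worth having whatever the table shows.

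Second, the scale. The planned summary is a risk ratio. Logistic regression yields an odds ratio. With an outcome expected in roughly one child in five, the two are not interchangeable, and a reader who sees both cannot separate the effect of adjustment from the change of scale.

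At stake are how clearly the result can be interpreted, which of two results is emphasised, and the precision that strong predictors already recorded could supply.

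**Working it through.** **1. The plan's own figure.** Sample size calculation uses "20% compared with 15% or 25% [25% lower or higher" (percentages impaired), "with 80% power and a significance level of 5% to be 1100 per group". With the two-proportion formula, pooled variance and a two-sided 5% test:

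n = [1.960·√(2·0.225·0.775) + 0.842·√(0.20·0.80 + 0.25·0.75)]² / 0.05² ≈ 1094 per group.

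This reproduces 1100. For 20% against 15% the same formula gives 906, so 1100 covers the larger case. The event rates below are therefore the plan's own.

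**2. Scale.** OR = [p₁/(1−p₁)] / [p₀/(1−p₀)] with p₀ = 0.20.

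- p₁ = 0.15 (RR 0.75): (0.15/0.85)/(0.20/0.80) = 0.706.
- p₁ = 0.25 (RR 1.25): (0.25/0.75)/(0.20/0.80) = 1.333.

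This is the change of scale alone, before any covariate enters.

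**3. Selection into the cohort.** Survivors: 1609 × 0.880 + 1602 × 0.843 ≈ 1416 + 1350 = 2766. The plan seeks 2200 of them, or 2200/2766 ≈ 80%. Survival differs by 88.0 − 84.3 = 3.7 percentage points. Relative to intervention-arm survivors, that is a net 3.7/88.0 ≈ 4% who would not have been expected to survive under control care. The article cannot show how far consent differs by arm.

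**4. How often the trigger would fire by chance.** Assume that important means p < 0.05 (the article does not say this) and that k independent covariates are perfectly randomised. P(at least one) = 1 − 0.95^k: 23% for k = 5, 40% for k = 10, 64% for k = 20.

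**5. Type I error of the rule.** A null simulation used 2000 replicates, 2200 infants, five sites with balanced arms and one prognostic covariate of assumed strength. The Monte Carlo standard error is about 0.5 percentage points.

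| Analysis | Type I error |
|---|---|
| Never adjusted | 5.1% |
| Always adjusted for the covariate | 4.8% |
| Adjusted only if the covariate differs at p < 0.05 | 5.0% |
| Better of the two results reported | 6.2% |
| Adjusted for site only | 5.6% |

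The simulation assumes sound randomisation, so it does not address imbalance created by survival or consent.

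**6. Siblings.** The article gives no share of infants in co-enrolled sets, no within-set correlation and no allocation rule. Assume twin pairs, a share m of 10–40% and a correlation ρ of 0.1–0.5.

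- Siblings in the same arm: design effect 1 + mρ = 1.01 to 1.20, true two-sided error 5.1% to 7.4% if pairing is ignored.
- Siblings in opposite arms: design effect 1 − mρ = 0.80 to 0.99, true error 2.8% to 4.9%.

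The sign depends on a fact that the article does not state.

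**The case against.** The strongest defence is that adjustment is described as additional. The unadjusted risk ratio is expressly primary when loss is 2.5% or lower, an unadjusted comparison of randomised groups is not an error, and the conditional rule keeps the type I error at its nominal level. The Cox half of the sentence is on the same scale as the planned hazard ratio, so the mismatch affects only the logistic half. The article is also a condensed account, and covariate lists and variance estimators are commonly left to the analysis plan.

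Much of this stands. It limits the size of the point but does not remove it. The trigger and the logistic model are stated, not left open. The primacy of the risk ratio is written only for loss of 2.5% or lower; above that, hazard ratios are added and the text does not say which result leads. The section on the assessment schedule reports lockdowns and permanent moves by families, so loss above 2.5% is plausible.

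A reader might go further and infer that the models leave out site and treat siblings as independent, so that the standard errors are wrong. The article does not support that. It is silent on these terms and does not exclude them. The sibling effect could run either way, and the simulation gave no sign that omitting site invalidates the test. The sites also share standardised tools, central training and monitoring. What can fairly be said is that country is named for imputation but not for the comparison, and that the handling of siblings is not described.

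**Conclusion.** The concern holds as a moderate, easily corrected weakness. The plan makes the existence of an adjusted result depend on an undefined judgement after the data are seen, in a cohort where imbalance may be real, and it gives the adjusted binary result on a scale that cannot be set directly beside the risk ratio (0.71 against 0.75, or 1.33 against 1.25, at 20% control risk).

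A reader might infer that the conditional rule inflates false positives. The working does not show this: the error is 5.0% under the rule and reaches 6.2% only if the better of two results is picked, which the text permits but does not plan. Nor is the odds ratio a biased test of the null; the problem is interpretation.

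The scale figures rest on the plan's own rates. The trigger frequencies rest on reading important as p < 0.05, the simulation on an assumed covariate effect, and the sibling ranges on assumed shares and correlations. The gain in precision is not quantified, because the article does not give the strength of the predictors.

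**What to change.** - Delete the imbalance condition and the logistic model.
- Prespecify one adjusted risk ratio for the primary composite, reported whatever the baseline table shows. Use modified Poisson regression (log link, robust variance) or log-binomial regression, with country or site, birth weight, gestational age and singleton/multiple status as covariates.
- Cluster the robust standard errors on the mother, because multiples are enrolled. State how siblings were allocated in the parent trial. Country or site belongs in the model as a fixed term.
- Put the same covariates in the imputation model.
- If hazard ratios are reported, give the Cox model the same fixed covariates.

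The cost is wording and slightly more analysis work. The plan already uses country, birth weight, gestation and multiplicity, so the only possible addition is a mother identifier that links siblings. Log-binomial models may fail to converge, which modified Poisson avoids. Fixed adjustment guards only against imbalance in the measured covariates; it does not remove all selection through survival or consent.
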